### Randomization and allocation concealment

After the baseline evaluation, each eligible participant was randomly assigned to either the intervention group or the control group at a 1:1 ratio. The random allocation cards will be generated using the random permutation principle with a random number table generated by SPSS21. These cards will be placed in opaque envelopes, with the envelope numbers corresponding to the card numbers. The envelopes will be opened in the order of the participants’ visits, and the participants will be randomly assigned to either the conventional rehabilitation group or the conventional rehabilitation combined with VR training group based on the grouping specified on the card inside the envelope. This method of random allocation will ensure that the assignment is unbiased and that each participant has an equal chance of being assigned to either group.

## Blinding

### Who will be blinded

For this trial, the individuals responsible for brain functional magnetic resonance imaging (fMRI) data collection and analysis were kept blinded. A physiotherapist who was involved in the treatment of spinal disorders and belonged to the same institution as the first author was the therapist. Patients, therapists, and evaluators were not blinded to the treatment group to which the patients had been allocated.

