### Procedure for unblinding

The unblinding procedure was conducted at the completion of the trial or at the specified endpoint. An independent unblinding committee composed of experts unrelated to the study was established. The committee members were blinded to the allocation of participants throughout the trial to maintain independence and objectivity. A detailed unblinding plan, including the timing, sequence, and identity verification process of unblinded participants, was developed and approved by the ethics committee of Yueyang Integrated Chinese and Western Medicine Hospital affiliated with Shanghai University of Traditional Chinese Medicine prior to trial initiation. Randomization codes and group assignments were securely stored by an independent data manager or committee member. The unblinding process was executed by members of the unblinding committee or by authorized individuals; this process involved the verification of participants’ group assignments and the provision of treatment codes or the decryption of treatment groups. After unblinding, the data analysts analysed the data and interpreted the trial results based on the unblinded data, including comparisons and assessments of statistical significance between the treatment and control groups.

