### Data collection and management

Initially, the screening personnel reviewed the inclusion and exclusion criteria and collected basic characteristic data prior to random allocation. Trained assessors, who are blinded to the allocation and not involved in the intervention, will play a crucial role in measuring the primary and secondary outcomes. The data for all participants will be recorded in a designed case report form (CRF). Additionally, each CRF will be checked twice to ensure the accuracy and completeness of the data collection throughout the study. All relevant documents will be coded with specific identification numbers and kept in a secure, locked box to safeguard the privacy and data safety of the subjects. The magnetic resonance scans obtained during the study will be saved on a computer with restricted access and a password known only to the principal investigator. The materials will be securely stored in compliance with medical records retention regulations and good clinical practice principles for 5 years after the trial. The study will also be monitored for safety by a physical therapist and two clinical doctors who are not involved in the research. The researchers will ensure that the study is conducted in compliance with standard operating procedures (SOPs), monitor the study’s progress, review all adverse events, and discontinue the trial if any measures cause significant adverse effects such as headache, nausea, or vomiting. The assessors reported any adverse events to the *data monitoring committee* (DMC) and the ethics committee of Yueyang Integrated Chinese and Western Medicine Hospital affiliated with Shanghai University of Traditional Chinese Medicine. DMC is independent from the sponsor and competing interests.

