### Statistical analysis

All nonimaging data will be analysed using SPSS version 21 by an independent statistician who is blinded to the treatment and control groups to ensure objectivity and reduce bias. The statistical significance level for testing will be set at 0.05 with a two-tailed test. Continuous variables are presented as the mean, standard deviation, or maximum or minimum values based on their statistical distributions. Independent sample *t* tests or nonparametric tests (Mann–Whitney *U* test) will be used to compare the results presented as continuous variables and mean values to validate the effectiveness of the intervention. Furthermore, intra- and intergroup comparisons were made at 4 weeks to observe the differences between the two intervention methods. If necessary, logistic regression, general linear correlation, or regression was used to compare different types of results based on the variable type and distribution. Basic data comparisons between the treatment and control groups will be performed using *t* tests, chi-square tests, or nonparametric tests. Participants who drop out during the intervention period will not be excluded according to the intention-to-treat principle, and missing data will be replaced using the last observation carried forward method to maintain statistical power and avoid bias.

The amplitude of low-frequency fluctuation (ALFF) is an indicator of the amplitude energy of the low-frequency spectrum and reflects the spontaneous activity of neurons in the resting state of the brain. The ALFF is a useful tool for analysing functional MRI data to study longitudinal neural changes and explore the relationship between brain plasticity and the recovery of sensory and motor function induced by stimulation [22]. In this study, the REST 1.9 software from Beijing Normal University (http://www.restfmri.net/) was used to perform linear drift and calculate the amplitude of signal oscillation in each voxel in the low-frequency range (0.01–0.1 Hz) to obtain ALFF images. Finally, the ALFF values of each participant were *Z*-transformed for further statistical analysis.

Longitudinal measurements in a resting-state task and further correlation analysis of imaging and scale score data obtained from baseline and postintervention measurements were performed to explore the relationships between brain remodelling and postoperative sensory and motor function recovery in CSM patients.

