## Discussion

CSM is the most severe type of cervical spondylosis, and in severe cases, it can lead to paralysis. Surgery is the only reliable solution for patients with advanced CSM who suffer from severe sensory and motor dysfunction, such as lower limb weakness, limb numbness, unstable gait, and limited fine motor activity of the hands. However, even after relieving the pressure on the spinal cord caused by prolonged compression, damaged nerve function may not fully and quickly recover. As a result, residual sensory and motor impairments after surgery can cause significant psychological stress. Rehabilitation is considered an important component of recovery in many neurological disorders, including stroke, traumatic brain injury (TBI), and spinal cord injury (SCI) [15, 23, 24]. Despite these findings, there has been a lack of clinical research promoting rehabilitation for CSM patients [25]. New evidence suggests that rehabilitation strategies may have a substantial impact on the recovery of CSM patients, and existing rehabilitative interventions for traumatic SCI and stroke may be applicable due to their similar pathophysiology [26]. Various rehabilitation methods can be used for the postoperative rehabilitation of patients with CSM, such as gait training, hand function training, and VR training. The latter is particularly interesting due to its multisensory stimulation, which promotes brain reshaping and functional recovery, integrating traditional gait training into more enjoyable VR training. Additionally, numerous technologies, such as transcranial magnetic stimulation (TMS) and transcranial direct current stimulation, have been rapidly developed as noninvasive neuroregulation techniques. These techniques have been widely used in the clinical treatment of various neurological disorders, such as stroke, spinal cord injury, Alzheimer’s disease, Parkinson’s disease, chronic pain, depression, and addiction, with promising results [27–29]. No relevant literature on postoperative neuroregulation treatments for CSM patients at the brain functional level have been found. However, we believe that using noninvasive neuroregulation techniques to purposefully regulate brain function after effective cervical spine surgery decompression could be highly important for improving its short-term efficacy and the long-term recovery of CSM patients. One potential limitation of this trial is that it was not a double-blind controlled trial. Although we attempted to blind everyone, this approach is not always feasible in nonpharmacological studies, and we cannot expect participants in the trial to pretend to be blind to the recovery treatment or to the therapists and clinicians [30]. However, throughout the trial, outcome assessors or statisticians will be blinded to the study design to eliminate any potential bias.

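### The protocol says both that evaluators know the allocation and that outcome assessors do not, so it does not settle whether the examiner-graded JOA primary outcome is scored blind.

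*Protocol article*

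**What the plan says.** Four sections of the protocol article bear on who knows the allocation.

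- **Who will be blinded.** The only role named as blinded is imaging: "the individuals responsible for brain functional magnetic resonance imaging (fMRI) data collection and analysis were kept blinded". For everyone else: "Patients, therapists, and evaluators were not blinded to the treatment group to which the patients had been allocated".
- **Data collection and management.** "Trained assessors, who are blinded to the allocation and not involved in the intervention" are the people who "will play a crucial role in measuring the primary and secondary outcomes".
- **Discussion.** After conceding that the trial is not double-blind, the article says that "throughout the trial, outcome assessors or statisticians will be blinded to the study design to eliminate any potential bias".
- **Procedure for unblinding and Statistical analysis.** The first says that after unblinding "the data analysts analysed the data and interpreted the trial results based on the unblinded data". The second assigns the non-imaging data to an "independent statistician who is blinded to the treatment and control groups".

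The primary outcome is change in the JOA score (Outcomes; Primary outcome measurement). It is assessed before the intervention, after it and during follow-up. Table 1 grades the score in verbal categories, many separated by half points.

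**The concern.** The section devoted to blinding denies what the data collection section and the Discussion assert. The JOA is graded by an examiner, who must decide, for example, whether chopstick use is awkward, whether gait is unsteady or whether numbness is slight. VR training is added to the same conventional programme, so patients and therapists cannot be blinded. A rater who does not know the arm is therefore the main remaining protection for the primary outcome.

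If evaluators do know the arm, any tendency to score one arm more favourably goes straight into the between-arm difference. The planning difference is 15.30 − 14.7 = 0.6 points, little more than one half-step on one item. Readers of the eventual report could not tell whether the protection claimed in the Discussion was in place.

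**Working it through.** **1. The statements side by side**

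| Section | Staff | Status |
|---|---|---|
| Who will be blinded | evaluators | know the allocation |
| Data collection and management | assessors of primary and secondary outcomes | blinded to allocation, not treating |
| Discussion | outcome assessors or statisticians | blinded, but to the study design |

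Could evaluators and assessors be different people? The non-imaging outcomes are the JOA, VAS and NDI. Imaging staff are already listed separately as blinded. The article describes no other evaluation task, so the natural reading of evaluators is the staff who score these scales. The Discussion does not settle the matter: its "or" leaves open which of the two groups is meant, and blinding to a study design is not blinding to allocation. All these statements are in current text.

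**2. Which JOA scores are exposed**

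Under Randomization and allocation concealment, assignment follows the baseline evaluation. Baseline raters cannot know the arm. The exposed scores are those at week 4 and at follow-up.

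**3. The plan's own figures (Sample size calculation)**

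- Pooled SD = √((0.90² + 0.78²)/2) = √(1.4184/2) = 0.842.
- d = 0.6/0.842 = 0.712; the plan states 0.71.
- A two-sided t test at 0.05 with 32 per arm has power 0.801, so the stated 64 reproduces.
- 32 × 1.2 = 38.4, rounded up to 39 per arm, gives the stated 78.

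**4. Illustration of what a rater lean would do**

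Assumptions: no true effect; unblinded raters favour one arm by an average of b points over all analysed participants; two-sided t test at 0.05. The rejection probability comes from the noncentral t distribution with 2n − 2 degrees of freedom and noncentrality (b/SD) × √(n/2). For example, b = 0.2, SD = 0.842 and n = 32 give 0.2375 × 4 = 0.95, and a rejection probability of 15.5%.

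| Lean b (points) | SD 0.842, n = 32 | SD 0.842, n = 39 | SD 1.5 (assumed), n = 39 |
|---|---|---|---|
| 0 | 5% | 5% | 5% |
| 0.1 | 7.5% | 8.1% | 6.0% |
| 0.2 | 15.5% | 17.9% | 9.0% |
| 0.3 | 28.9% | 34.2% | 14.1% |

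The 39-per-arm columns match the stated analysis, which keeps dropouts under intention to treat with last observation carried forward. A participant whose baseline score is carried forward contributes no rater lean, so b in those columns must be read as an average that includes such participants.

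**The case against.** The strongest case on the other side has four parts.

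**The data collection section may describe what is done.** It is specific: trained, non-treating, blinded assessors. The sentence in the blinding section may then be only a drafting error. That is possible, and a reader should not infer that the JOA is certainly scored unblinded. But the opposite is equally open: the blinding section is the dedicated one, it is in the past tense, and recruitment began in June 2023. The text does not decide between them, so the contradiction stands.

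**The percentages are not properties of this trial.** This stands. The size of the lean is assumed. The SD of 0.84 is of one-month scores in a pilot of 10 per arm, whereas the outcome is change, whose SD is not given. A reader might infer that the trial's false-positive rate is 29% or 34%. The documents do not support that: the figures apply only if evaluators are unblinded and lean by the assumed amount, and they are much smaller at a larger SD.

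**The analyst wording is a lesser matter.** A reader might see the blinded statistician and the unblinded data analysts as the same contradiction again. They may be different people or successive steps, and unblinding after data collection cannot alter a JOA score already recorded. What remains is that the unblinding section places significance testing after decoding, which fits poorly with the Statistical analysis section.

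**The article admits the lack of double-blinding.** It does so as a limitation that concerns participants, therapists and clinicians. In the same place it claims blinded outcome assessors, so the admission does not cover the point.

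**Conclusion.** The contradiction is real and must be resolved. Evaluators cannot be both unblinded and blinded when they score the post-randomisation JOA, and this concerns the rater of the primary outcome. A separate analysis plan would not settle it, because who rates and what they know is trial conduct.

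Its consequence depends on which statement is true. If the assessors are blinded, the harm is a reporting error in the blinding section. If they are not, the primary comparison is open to detection bias. As an illustration, leans of 0.2 and 0.3 points would raise the false-positive rate from 5% to between about 9% and 18%, and between about 14% and 34%, across the two SDs considered with 39 per arm. These ranges rest on an assumed lean and, at the lower end, an assumed SD of change of 1.5.

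Two limits apply. Baseline scoring is not affected. And blinded raters would not remove bias from what unblinded patients report in the VAS, the NDI and the sensory and bladder items of the JOA, so the Discussion's claim that blinding removes all potential bias is too strong even if the assessors are blinded.

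**What to change.** First establish how the JOA has been scored since recruitment began.

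1. **From now on.** Have every post-randomisation JOA, at week 4 and at follow-up, scored by the non-treating, allocation-blinded assessors described under Data collection and management. State under Who will be blinded that only patients and therapists are unblinded. Ask patients not to reveal their arm, and record each assessor's guess of allocation. Baseline scoring needs no change.
2. **If unblinded raters have already scored participants.** Correct the data collection section and the Discussion to say so, flag those records, run a sensitivity analysis on the primary comparison, and withdraw the claim that blinding eliminates bias.
3. **In either case.** Add to the Discussion that rater blinding does not protect patient-reported content.
4. **Secondary.** Align Procedure for unblinding with Statistical analysis: run the primary comparison on arms coded A and B, and decode afterwards.

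The cost is a protocol amendment, scheduling of assessors and one extra item on the case report form. No new role is needed if the blinded assessors exist as described; if they do not, they must be provided. Sample size, outcomes and treatment are unchanged.

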### Procedure for unblinding

The unblinding procedure was conducted at the completion of the trial or at the specified endpoint. An independent unblinding committee composed of experts unrelated to the study was established. The committee members were blinded to the allocation of participants throughout the trial to maintain independence and objectivity. A detailed unblinding plan, including the timing, sequence, and identity verification process of unblinded participants, was developed and approved by the ethics committee of Yueyang Integrated Chinese and Western Medicine Hospital affiliated with Shanghai University of Traditional Chinese Medicine prior to trial initiation. Randomization codes and group assignments were securely stored by an independent data manager or committee member. The unblinding process was executed by members of the unblinding committee or by authorized individuals; this process involved the verification of participants’ group assignments and the provision of treatment codes or the decryption of treatment groups. After unblinding, the data analysts analysed the data and interpreted the trial results based on the unblinded data, including comparisons and assessments of statistical significance between the treatment and control groups.

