#### Primary outcome measurement

The primary outcome measure was the change in the JOA score for the cervical spine. The JOA score consists of a total of 17 points, with 4 points each for upper and lower limb motor function, 2 points each for upper and lower limb and trunk sensation, and 3 points each for bladder function. Patients were assessed using the JOA score before intervention, after intervention, and during follow-up in accordance with the JOA evaluation criteria for cervical spine disease treatment established by the Japanese Orthopaedic Association. The results were categorized into five groups: > 75% excellent, 50–74% good, 20–49% fair, 0–19% no change, and < 0 deterioration.

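### The article places the between-arm tests after unblinding in one section and assigns them to a blinded statistician in another; both cannot hold for the primary analysis

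*Protocol article*

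**What the plan says.** Four places in the protocol article bear on whether the analyst knows the arms.

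- **Procedure for unblinding.** Unblinding takes place when the trial is complete or at a specified endpoint. The section then says: "After unblinding, the data analysts analysed the data and interpreted the trial results based on the unblinded data". It spells out the scope of that work: "including comparisons and assessments of statistical significance between the treatment and control groups".
- **Statistical analysis.** All nonimaging data are to be analysed "by an independent statistician who is blinded to the treatment and control groups to ensure objectivity and reduce bias".
- **Discussion.** As an answer to the lack of double blinding, it says that "outcome assessors or statisticians will be blinded to the study design to eliminate any potential bias".
- **Who will be blinded.** The people responsible for "brain functional magnetic resonance imaging (fMRI) data collection and analysis were kept blinded". The same section says that patients, therapists and evaluators are not blinded.

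The primary endpoint is a nonimaging one: "The primary outcome measure was the change in the JOA score for the cervical spine".

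**The concern.** One section reveals the arms first and tests afterwards. Another has the same tests done by someone who does not know the arms. A reader cannot tell which will happen, and a later report could cite either.

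This matters because the trial has few other protections against expectation. Patients and therapists know the allocation. Blinding of the outcome assessors is itself stated both ways: Who will be blinded says that evaluators are not blinded, while Data collection and management and the Discussion say that assessors are. Analyst blinding is therefore one of the few safeguards left to claim, and the Statistical analysis section claims it expressly as a protection against bias. If the unblinding section describes what will be done, that claim is untrue.

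**Working it through.** No arithmetic applies, and the plan gives no figure on this point to reproduce. The check is whether the passages can be read together.

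**Step 1: which data are covered.** The outcomes are JOA, VAS, NDI and fMRI. The first three are nonimaging, so the Statistical analysis section gives them to the blinded statistician. The fourth falls under the blinded fMRI analysis in Who will be blinded. Between them, these two statements cover every primary and secondary outcome and leave no efficacy comparison for analysts who know the arms.

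**Step 2: what the unblinding section assigns.** It gives its analysts the between-arm comparisons and significance tests, done after unblinding. It does not limit this to supplementary or safety analyses. By Step 1, these are comparisons that another section has already placed under blinding. For the JOA change, the two statements are in direct conflict.

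**Step 3: readings that might reconcile them.**

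| Reading | Does the text allow it? |
|---|---|
| Two steps: coded analysis first, then labels revealed for interpretation only | No section describes this. The unblinding section puts both analysis and interpretation after unblinding. |
| The codes released are only A/B labels, so the analyst stays blind | Unlikely. The section offers decryption of the groups as the alternative and then calls the data unblinded. |
| The analysts and the independent statistician are different people with different tasks | This would help only if the analysts did no between-arm testing, but the section says that they do. |
| Blinding was meant to last only until database lock | The Statistical analysis section attaches the blinding to the person doing the analysis, so it has to last through the analysis. |

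None of these removes the conflict as written.

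**Step 4: weight of the other two places.** The Discussion points the same way as the Statistical analysis section, but loosely: it says assessors or statisticians, and describes them as blind to the design rather than to the groups. The fMRI statement conflicts with the unblinding section only if the data mentioned there include imaging, which that section does not say. The firm contradiction is therefore the one on nonimaging data.

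**The case against.** The strongest reply is that an article condenses. The unblinding section mentions a detailed, ethics-approved plan covering timing and sequence. That plan is not shown and may set out a coded analysis before the labels are released. This is a fair reason not to conclude that the trial will be analysed unblinded. It does not rescue the text: the article affirmatively states two incompatible rules, and one must be corrected whatever the plan says.

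A second reply is that this is a wording matter in a study that calls itself exploratory, with no demonstrated numerical effect. That stands as a limit on severity. It does not make the blinding claim accurate.

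A reader might also infer three stronger points, which the documents do not support.

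- **That an open choice of test lets knowledge of the arms inflate the type I error.** The article does say "Independent sample *t* tests or nonparametric tests (Mann–Whitney *U* test) will be used to compare the results", and later "If necessary, logistic regression, general linear correlation, or regression was used to compare different types of results". But a statistical analysis plan that is not shown may name the test. The regression sentence goes on to tie the choice to variable type and distribution. Moreover, a two-sided p-value is the same whether the arms are called A and B or by name, so an analyst on coded arms could equally pick the smaller p. Prespecification cures that problem and blinding does not. An error rate for the choice of test would not measure this conflict.
- **That no blinding exists at all.** Unblinding comes only at trial completion or a specified endpoint, so the conflict does not touch blinding before then, including during fMRI data collection.
- **That brain regions or outliers would be selected with the arms known.** The article describes no step at which either is selected.

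**Conclusion.** The point holds as a contradiction about analyst blinding. The unblinding section and the Statistical analysis section cannot both govern the JOA primary analysis or the VAS and NDI comparisons, and no passage reconciles them. If the former is followed, the safeguard claimed in the latter, and echoed in the Discussion, is untrue.

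The size of any resulting bias cannot be computed from the document, and no figure should be attached. The sample size (64, or 78 with the dropout allowance) does not depend on it. The conclusion rests only on the wording of the article. It assumes that the data in the unblinding section include the nonimaging outcomes, which follows from that section's reference to significance tests between the arms. The extension to fMRI is less certain because that section does not mention imaging. The correction should be made before the final analysis.

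**What to change.** Rewrite the end of Procedure for unblinding so that the order is:

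1. The database is locked.
2. The prespecified primary and secondary analyses are run on arms coded A and B. Fields that reveal the arm stay out of that file. One example is adverse-event entries naming intolerance of VR training, which Safety assessment says will be recorded; these can be analysed after the codes are released.
3. The results are declared final.
4. Only then does the independent code-holder already described in that section (a data manager or committee member) release the codes.

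Apply the same order to the fMRI group analysis, and check that the ethics-approved unblinding plan says the same.

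If the analysis really will be unblinded, the alternative is to leave the unblinding section as it is and withdraw the blinded-statistician claims in Statistical analysis and the Discussion. The fMRI statement would then need the same check.

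The cost is a few sentences, a coded data export and an amendment submitted to the ethics committee as Protocol amendments requires. The sample size, visits and outcomes do not change. The article reports recruitment as ongoing at submission, so on its own timeline the order could be settled before the final analysis.
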